### Confounders and Bias

Possible confounders include gender [28] and BMI [29]. Moreover, it is likely that tumor stage and type may influence the results of this study. Therefore, we will examine these factors and adjust our interpretations accordingly. Furthermore, the nature of our website (which highlights the benefits of vegetarian and vegan diets) might attract a population that actively seeks healthy lifestyle habits [27]. Conversely, this group might prefer alternative therapies, and be less compliant to conventional oncological therapies. Therefore, we plan to undertake a subanalysis for treatment groups (oncological treatment followed, oncological treatment rejected, or oncological treatment completed).

### Nutrition Safety

To ensure timely detection of the deterioration of nutritional and/or health status of the patients in this study, an intermediate data evaluation is planned, and will include all participants registered before January, 2016. This evaluation will examine tumor staging and the nutritional status of all participants. If this evaluation demonstrates a significantly increased risk of health deterioration in one diet group compared to the omnivorous group, the study will be stopped preterm.

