### Eligibility and Recruitment

Patients were eligible for this study if they were diagnosed with cancer, >18 years of age, and were included in a tumor treatment regime or a follow-up program. Exclusion criteria included psychiatric treatment during the previous 3 months, pregnancy, breastfeeding, BMI below 18 kg/m^2^, major difficulties with food intake (eg, swallowing, lack of appetite), and participation in other studies requiring the use of a special diet.

Potential participants were recruited online (via the study website, Facebook, online reports, and television and media reports) and offline (via clinical practices, oncological departments, and associations supporting cancer patients). Recruitment took place between April, 2015 and June, 2016.

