### Statistical Analyses

Statistics regarding safety issues will be performed in July, 2016 and a complete evaluation will be performed in January, 2017. Comparison of dietary groups in regard to primary and secondary end points will be performed as ITT. Data will be analyzed and adjusted for possible confounders (eg, gender, age, tumor type, tumor stage, weight status, accompanying treatment) and stratified by sex, age, type of tumor, tumor staging, and oncological therapy. Changes over time (eg, weight changes) will be analyzed by paired sample tests. Unpaired tests will be used when making comparisons between cohorts. Descriptive statistics will be used to summarize parameters such as comorbidities, oncological therapies, and additional therapies. *P*-values of <0.05 will be considered significant.

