### Recruitment and Dropout Rates – Preliminary Experiences

As of May, 2016, 530 participants filled out the checklist and 242 (45.7%) have registered for the study. Most respondents were female (174/242, 71.9%), while 68 were male (28.1%). Mean age was 54.7 years (standard deviation 11.7). Most participants were recruited in German speaking countries (Germany, Austria, and Switzerland). As shown in Figure 1, most participants found the website via the Internet or social media (eg, Facebook and Twitter).

Dropouts occurred at each stage of the study, from the checklist for eligibility to the third data survey, as shown in Figure 2. After filling out the registration forms, 242 participants received the invitation for their first data survey, which was completed by 138 respondents (57.0%). Some respondents (33/242, 13.6%) sent an incomplete survey, and 68 of the original participants (28.1%) did not send a survey. Dropout rates consider participants who withdrew study participation, died, or did not answer after being reminded by email. Four patients have been reported to have died as of May, 2016.

Three months after completing the first survey, participants received an invitation for the second survey (n=109 as of May, 2016), which was completed by 72 respondents (66.1%). Four participants (4/109, 3.6%) sent an incomplete survey and 33 (30.3%) dropped out of the study at this point. The study is still underway, and participants who did not receive the second and/or third surveys have been excluded from these calculations.

The 6-month data survey was sent to 43 participants who completed the first and second surveys. As of May, 2016, this survey was completed by 33 participants (77%); 2% (1/33) sent an incomplete survey, and 21% (9/33) dropped out of the study at this point. Given the number of participants who enrolled in the study at least 6 months before May, 2016 (n=101), this gives a completers rate of 32.7%.

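### The only dated safety analysis comes after recruitment closed and leaves out the participants still on a study diet, which does not fit the promised timely detection and early stop

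*Protocol article*

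**What the plan says.** The Nutrition Safety section gives the purpose of the evaluation: "To ensure timely detection of the deterioration of nutritional and/or health status of the patients in this study". The population is fixed by registration date: "an intermediate data evaluation is planned, and will include all participants registered before January, 2016". On content it says: "This evaluation will examine tumor staging and the nutritional status of all participants". The consequence follows if the evaluation shows a "significantly increased risk of health deterioration in one diet group compared to the omnivorous group, the study will be stopped preterm". The section does not say when the evaluation takes place.

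The date is given under Statistical Analyses: "Statistics regarding safety issues will be performed in July, 2016 and a complete evaluation will be performed in January, 2017". The Results paragraph of the abstract agrees, placing a preliminary safety evaluation after June 2016. Eligibility and Recruitment states: "Recruitment took place between April, 2015 and June, 2016". Study Population and Setting has participants keep the chosen diet for 6 months and provides an online form for reporting severe deterioration.

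The preliminary report on recruitment and dropout says: "Dropout rates consider participants who withdrew study participation, died, or did not answer after being reminded by email". It also reports four deaths by May 2016, without diet group.

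**The concern.** An interim safety look can do three things: halt enrolment, change what happens to the people whose data are examined, or change what happens to others still exposed. On the article's own dates the first is ruled out and the second nearly so. The third remains, but the data of the people it would serve are left out.

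Content is a second matter. Staging and nutritional status come from questionnaires, uploaded reports and laboratory results. A participant who dies or becomes too ill to answer may supply neither. If such events are not brought in from another source, a diet group that fares worse could lose its worst cases from the comparison. The article itself names the safety of vegan diets in cancer patients as a concern, so what a reassuring result would mean matters here.

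**Working it through.** **Inputs from the article.** Recruitment runs from April 2015 to June 2016. The evaluated set is those registered before January 2016, so the last possible date is 31 December 2015. The diet period is 6 months. The safety statistics are in July 2016. By May 2016, 242 had registered, 101 had enrolled at least 6 months earlier, 33 had completed the 6-month survey and four had died.

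**Step 1: enrolment.** Recruitment ended in June 2016 and the look is in July 2016. No enrolment is left to stop.

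**Step 2: those evaluated.** End of diet period = registration + 6 months.
- First registrants: 1 April 2015 + 6 months = 1 October 2015, about nine months before the look.
- Last registrants in the set: 31 December 2015 + 6 months = 30 June 2016, before the look.

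The survey clock starts at the first survey, not at registration. The article does not give the lag. Assuming 2, 4 or 8 weeks, the last end date moves to 14 July, 28 July or 25 August 2016. A few late-December registrants could therefore still be on the study diet.

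**Step 3: those left out.** Registration on 31 January 2016 gives an end date of 31 July 2016, and on 30 June 2016 gives 30 December 2016. The participants with diet time still to run in July 2016 are thus mainly the 2016 registrants, whose data are excluded by the registration cut.

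**Step 4: how many.** 242 − 101 = 141, and 141/242 = 58.3%. The 101 had enrolled by about November 2015, whereas the evaluated set runs to the end of December 2015. Registrants from about November and December 2015 are therefore among the 141 but inside the set, so 141 is an upper bound on those excluded by May 2016. The exact number is not given. Anyone registered between the May count and the close of recruitment would come on top.

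**Step 5: events and attrition.** The article's completers rate reproduces: 33/101 = 32.7%. Known deaths are 4/242 = 1.7% of registrants. About two thirds of those enrolled long enough had no completed 6-month survey, so deaths and severe illness have to reach the comparison by another route. Nutrition Safety names none.

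**Illustration only.** The article gives neither cohort sizes nor deterioration rates. With two-sided 5% tests and 15 to 35 evaluable per group (assumed), power is 0.11 to 0.21 for 10% against 20%, and 0.27 to 0.55 for 10% against 30%. With 25 per group and 20% against 60%, it is 0.79 (Fisher) to 0.87 (chi-square). Under these assumptions the look could find a very large harm but would often miss a moderate one.

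**The case against.** Several counter-arguments deserve weight.

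- **The link between the two sections is an inference.** Nutrition Safety gives no date, and the figure showing the planned evaluations is not available here. An earlier look may have been intended. This stands as a caveat, but the article dates no other safety analysis before the complete evaluation in January 2017, so the text still needs reconciling.
- **Restricting the set to mature data is defensible.** Participants with about 6 months of follow-up give a cleaner comparison. That is a fair reason to show them separately. It does not justify leaving out what is already known about people still on a diet.
- **The look is not useless.** A reader might infer that it can protect nobody. The documents do not support that: a stop in July 2016 could still help 2016 registrants and a few late starters. The article also envisages diets kept for longer than 6 months, and it follows participants at 12 and 24 months.
- **Deaths.** A reader might infer that the safety evaluation itself counts deaths as dropout. No section says so. The pooling belongs to the attrition report, which discloses the four deaths, and survival for end stages is a secondary outcome. Nor does the article say that the severe-deterioration forms go unused; it does not say how they enter the evaluation.
- **Detail left elsewhere.** The exact definition of the trigger, the test and multiplicity control may sit in a fuller document, and adjustment for tumor stage is already planned. None of these is part of this point.

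**Conclusion.** The point holds as a conflict of dates and population. An evaluation presented as timely, with power to stop the study, is dated after recruitment closed. It covers people whose diet period is over, apart from a few with a late first survey, and omits those still exposed. The omitted group is at most 141 of the 242 registered by May 2016 (58.3%). The true number is smaller by the registrants of about November and December 2015.

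The conclusion assumes that the evaluation described under Nutrition Safety is the one dated July 2016, and that the diet period runs from about registration.

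The point about deaths is weaker but still worth acting on. The evaluation does not name death, and completion is low, so deaths and severe deterioration could be missed. The documents do not show that they will be. The power figures are illustrations under assumed rates and carry none of the conclusion; they only show why a non-significant difference would not establish safety.

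**What to change.** 1. Reconcile the abstract, Eligibility and Recruitment, Nutrition Safety and Statistical Analyses on three things: when the safety evaluation takes place, whose data it uses, and what action it can still trigger at that date. The investigators have to settle the stopping rule itself; no rule is proposed here.
2. In the safety analysis, include all available data from everyone registered at the data cut-off. Participants with 6 months of follow-up can be shown separately. If the July 2016 look has already been run on the restricted set, repeat it on the wider set with the complete evaluation in January 2017.
3. Report deaths and severe-deterioration reports by diet group, alongside tumor staging and nutritional status.
4. Give each difference from the omnivore group with a confidence interval, and state that a non-significant result is not evidence of safety.

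The cost is wording changes and slightly more analysis, mostly on data already collected. The drawbacks are less mature data for recent registrants and a more cautious safety statement.

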### Feasibility, Physical Tolerance, and Acceptance of Chosen Diet

Feasibility of the protocol will be examined by (1) assessing compliance with the chosen diets at the 3 and 6-month time points, (2) asking the study participants to report any intermediate changes of the planned diet, and (3) specific questions contained in the questionnaire regarding the ease or difficulties of the diet, and support from family members and medical staff (Multimedia Appendix 4).

Physical tolerance will be examined via questions regarding physical symptoms. Acceptance will be examined via questions regarding ease, difficulties, and willingness to continue their diet until the study is completed and thereafter (Multimedia Appendix 4).

### Online Platform Performance

Prior to the recruitment phase, the study platform (checklist, registration) and surveys were tested by four patients, and adaptations were made according to their feedback. As shown in Multimedia Appendix 4, the performance of the online platforms (webpage platform, survey platform) was assessed via questions regarding users’ experience with the platforms, and with the questionnaires (eg, technical performance, ease of understanding the questionnaires, significance of content). Moreover, it was possible to evaluate time spent filling in the questionnaires, dropout rates between and within the questionnaires (incomplete questionnaires), webpage user statistics, and user characteristics such as time spent reading web content, favorite web content, and user interactions.

### Nutrition Data Validity

As shown in Multimedia Appendix 4, self-selected dietary patterns will be cross-referenced via FFQ. Moreover, laboratory parameters will include albumin, urinary pH, blood urea nitrogen, and hematocrit. It was not possible to control for additional vitamins, such as vitamin C. Questions regarding motivation and intention to choose a certain dietary pattern will serve as data to further support the validity of the trial, or reveal potential inconsistencies.

### Data Safety

Online data safety was a priority in the development of this study, and we strictly separated participants’ personal data (used for communication) from anonymous health/disease related data. To ensure anonymity, each participant received a personal login and study identification number. Administrative (personal) data were collected and stored on servers with enhanced security features. Password-restricted logins and Secure Sockets Layer-encrypted data transmission were used, and host server providers were required to sign a contract according to the German Bundesdatenschutzgesetz [30] to guarantee state-of-the-art handling, storage, and deletion of personal data. Health-related data were collected and hosted at Survey Monkey [31], using anonymous study questionnaires on a server compatible with the Health Insurance Portability and Accountability Act.

### Statistical Analyses

Statistics regarding safety issues will be performed in July, 2016 and a complete evaluation will be performed in January, 2017. Comparison of dietary groups in regard to primary and secondary end points will be performed as ITT. Data will be analyzed and adjusted for possible confounders (eg, gender, age, tumor type, tumor stage, weight status, accompanying treatment) and stratified by sex, age, type of tumor, tumor staging, and oncological therapy. Changes over time (eg, weight changes) will be analyzed by paired sample tests. Unpaired tests will be used when making comparisons between cohorts. Descriptive statistics will be used to summarize parameters such as comorbidities, oncological therapies, and additional therapies. *P*-values of <0.05 will be considered significant.

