**Results:**

The study was performed between April, 2015 and June, 2016, and a preliminary evaluation of safety aspects was undertaken after June, 2016. Primary and secondary outcomes will be evaluated when the final patients complete the study in December, 2016.

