## Methods

### Study Design

This is a prospective, longitudinal, and observational cohort study of cancer patients with four cohorts: (1) omnivore diet, (2) lacto-ovo-vegetarian diet, (3) vegan diet, and (4) other diets (see Table 1). All four cohorts will complete online questionnaires including a baseline assessment and follow-up assessments at 3 and 6 months (Figure 2). At the 12 and 24 month time points, participants will be contacted via email to complete a truncated study questionnaire.

**Table 1 table1:** Definition of dietary patterns.

Cohort	Meat & fish	Milk & dairy products	Eggs	Honey	Plant products
Omnivore diet	+	+	+	+	+
Lacto-ovo-vegetarian diet	-	+	+	+	+
Vegan diet	-	-	-	-	+
Other diets	Those that do not correspond to any of the above				

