### Study Population and Setting

Whenever possible, participants selected one of three defined diets (omnivore, lacto-ovo-vegetarian, or vegan) at baseline. If none of these diets was applicable, participants were classified as having *other diets* (Table 1). Participants were instructed to maintain the chosen diet for 6 months. In addition, respondents were encouraged to continue their prescribed cancer treatment during the study period, and to undergo all recommended follow-up investigations.

Calculation of the required sample size for this study is not possible, as the effect size of the dietary patterns is unknown. Therefore, this study is classified as a pilot study.

The study is being conducted online via a bilingual study website [27]. Registration processes, eligibility assessments, and questionnaires at baseline and follow-ups are all completed online between April, 2015 and December, 2016. Prior to study participation, potential participants performed an online eligibility check (Multimedia Appendix 1), and were asked to provide contact information and a signed patient information and consent form. After registration, participants received an email including their personal login information for the study website, their study identification number, and a link to their baseline questionnaire. Invitations for assessments at 3, 6, 12, and 24 months are delivered by email (Figure 2). If participants do not fill in their questionnaires at the respected time, they are sent reminder emails. In addition to the three main study questionnaires, study participants are asked to report any severe deterioration, unplanned change of their selected diet, or withdrawal from study participation, via online forms (Multimedia Appendix 2).

Ethical approval was obtained from the Ethics Committee of the City of Vienna on February 2nd, 2015 (EK 15-021-VK_NZ).

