### Measures and Evaluation Procedures

The primary outcome of this study is defined as complete tumor remission, and calculated as the rate of complete remissions at 6 months by intention-to-treat (ITT) analysis.

Secondary outcomes include tumor history, further classifications of tumor behavior (complete remission, partial remission, no change, or progression), relapse-free time (in months), survival rates for end stages, previous and current tumor therapies (including tolerance and side effects), comorbidities (eg, high blood pressure, stroke), as well as medications unrelated to the tumor (including dosage and intake plan). The determination of tumor behavior during the study period will be evaluated by two investigators, each using independent radiological and laboratory reports.

Data regarding previous nutritional history, the chosen diet during study participation, acceptance and feasibility of the chosen diet, frequency of dietary pattern change, extent and duration of nutritional changes, and the type and strength of support for nutritional changes will also be assessed. In addition, during baseline and follow-up surveys, adherence to dietary patterns will be cross-referenced by food frequency questionnaires (FFQs), which were specifically adopted for discrimination of plant- and animal-derived foods. Participants were also asked to self-report any unplanned change in diet during study participation. Nutritional status of participants will be evaluated using body weight (kg), BMI (kg/m^2^), laboratory test results (eg, albumin), and questions referring to eating problems. Results referring to nutrition and dietary patterns will be evaluated in terms of change and duration of change in dietary patterns (in months).

Study questionnaires also contain questions referring to quality of life covering the Karnofsky Index, as well as additional dimensions (ie, psychosocial wellbeing, psychosocial support). Online questionnaires were designed to be self-instructive and self-evident (Multimedia Appendix 3). In order to evaluate these parameters, questions pertaining to the study platform and interaction with the study team were also included in the questionnaires. The list of parameters included in the study questionnaire was designed to examine all study objectives, and is detailed in Multimedia Appendix 4.

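### The evaluation called complete is set for January 2017, before any 24-month contact can occur, and no censoring-aware method or time origin is stated for relapse-free time and survival

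*Protocol article*

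**What the plan says.** All references are to the protocol article.

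- **Recruitment** (Eligibility and Recruitment): "Recruitment took place between April, 2015 and June, 2016".
- **Follow-up schedule** (Study Design): "At the 12 and 24 month time points, participants will be contacted via email to complete a truncated study questionnaire". Study Population and Setting agrees: "Invitations for assessments at 3, 6, 12, and 24 months are delivered by email".
- **End of data collection** (Study Population and Setting, same paragraph): "questionnaires at baseline and follow-ups are all completed online between April, 2015 and December, 2016".
- **Evaluation date**: the Abstract states "Primary and secondary outcomes will be evaluated when the final patients complete the study in December, 2016". The opening of the Results section also puts completion in December 2016, and Statistical Analyses adds that "a complete evaluation will be performed in January, 2017".
- **Outcomes**: the primary outcome is the rate of complete remission at 6 months. The secondary outcomes in Measures and Evaluation Procedures include "relapse-free time (in months), survival rates for end stages", with no time origin and no horizon. The study aims at the end of the Introduction name the relapse-free interval as one of three measures of improved prognosis.
- **Method**: Statistical Analyses compares the dietary groups on primary and secondary end points and says "Unpaired tests will be used when making comparisons between cohorts". Adjustment and stratification use a list of examples in which time since diagnosis does not appear.

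**The concern.** The article plans contacts at 12 and 24 months, but its stated end of data collection and its final evaluation both come before the first 24-month contact. Read literally, the longest follow-up has no place in the analysis. Relapse and survival are the outcomes for which long follow-up matters most.

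The same dates fix how relapse-free time and survival would be compared in January 2017. Entry is staggered over 15 months, so participants will have been followed for very different lengths of time, and many will not have relapsed or died. Such times are censored. The only between-cohort method the article states is unpaired tests, without saying which. Participants may also enter while on treatment or in a follow-up program, with no limit on time since diagnosis, so the starting point of the clock matters. At stake is whether a cohort difference in one of the hypothesis-defining outcomes reflects diet, or reflects when people enrolled and how long before that they were treated.

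**Working it through.** **Inputs from the article:** first recruitment April 2015; last recruitment June 2016; completion December 2016; evaluation January 2017; contacts at 3, 6, 12 and 24 months. Arithmetic is in whole calendar months from enrolment. If the baseline survey follows registration with a delay, the later contacts move later still.

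1. **The plan's own date.** June 2016 + 6 months = December 2016. The stated completion date is reproduced, so it is the end of 6-month follow-up.
2. **24-month contacts.** April 2015 + 24 = April 2017 (earliest); June 2016 + 24 = June 2018 (last). To reach 24 months by January 2017 a participant would have had to enrol by January 2015, before recruitment opened. The share with 24-month data is 0%.
3. **12-month contacts.** The last falls in June 2017 (June 2016 + 12). Enrolment by December 2015 gives 12 months by December 2016, and enrolment by January 2016 gives 12 months by January 2017. If accrual was uniform over the 15 months (assumption), the shares are 9/15 = 60% and 10/15 = 67%. A rough check uses the 101 participants enrolled at least 6 months before May 2016 and the 242 registered by May 2016: 101/242 = 42%. This assumes that the two counts share a denominator, and its cut-off is a month or two early.
4. **Length of follow-up.** At December 2016: 6 months (June 2016 entrants) to 20 months (April 2015 entrants). At January 2017: 7 to 21 months.
5. **Extent of censoring.** The article gives no relapse rate. Assume that a fraction r relapses within 2 years at constant hazard; the fraction relapsed by month t is then 1 − (1 − r)^(t/24). For r = 10%: 3.0% at 7 months and 8.8% at 21 months. For r = 40%: 13.8% and 36.0%. Between 64% and 97% of times would then be censored, before any dropout is counted.
6. **What an ordinary test would do.** A simulation with no true difference used 4000 runs, 60 per cohort, exponential relapse times, follow-up uniform from 6 to 21 months and a 0.05 level; all of these settings are assumptions. It compared a Welch t-test on observed months with a log-rank test.

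| Median time to relapse | Accrual | t-test rejects | log-rank rejects |
|---|---|---|---|
| 12 months | alike | 5.1% | 4.6% |
| 24 months | alike | 5.0% | 5.2% |
| 48 months | alike | 5.0% | 4.9% |
| 12 months | one cohort in later half only | 53% | 5.4% |
| 24 months | one cohort in later half only | 88% | 5.2% |
| 48 months | one cohort in later half only | 99% | 5.2% |

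The later-half cohort had follow-up from 6 to 13.5 months. The excess comes entirely from unequal follow-up. Cohorts of 60 are generous: 138 completed baseline surveys in May 2016, split evenly, give 138/4 = 34.5 per cohort. Smaller cohorts or a milder imbalance would inflate the error less.

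**The case against.** The strongest reply is that the main study ends at 6 months. The primary outcome is fixed there, three main questionnaires are described, the 12- and 24-month contacts are truncated, and the data list in the Appendix covers baseline and months 3 and 6. January 2017 then fits, and the article never ties relapse-free time or survival to 24 months. This stands as far as the 6-month analysis goes. It does not remove the conflict between the scheduled later contacts and a questionnaire window that closes in December 2016, and a separate analysis plan could not remove it without changing one of the stated dates.

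Three stronger readings are tempting, and the article does not support them:

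- **That the tests ignore censoring.** No test is named. The sentence mainly separates between-cohort from within-person comparisons, a log-rank test also compares independent groups, and an unseen analysis plan may specify one. What can be said is that no censoring-aware method is stated.
- **That time since diagnosis is ignored and the comparison is biased as written.** The confounder list is given as examples, tumor history and previous therapies are collected, and a subanalysis by treatment status, including completed treatment, is planned. No time origin is stated. The claim that a one-year difference between cohorts in time since treatment becomes a spurious 12 months holds only if months are counted from treatment.
- **That the later data are never used, or that nearly all times are censored.** Some 12-month data can enter the January 2017 evaluation; only the 24-month data cannot. Under the assumed 40% two-year relapse, more than a third of the earliest entrants would have relapsed by 21 months.

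**Conclusion.** The date conflict is exact and needs no assumption beyond calendar arithmetic: the January 2017 evaluation comes three months before the earliest possible 24-month contact and 17 months before the last. It can include 12-month data from only part of the participants, 60% to 67% under uniform accrual and roughly 42% by the cruder count.

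The point about method is conditional. Follow-up of 7 to 21 months makes censoring certain in practice, and the article states only unnamed unpaired tests and no time origin. If an ordinary unpaired test on observed months were used, and cohorts differed in enrolment date (or in time since treatment, if the clock starts there), a spurious difference could arise. The article gives no enrolment dates by cohort, so the size in this study is unknown; with similar accrual the simulated t-test kept its 5% level. The 6-month primary outcome is not affected. The matter should be corrected because the relapse-free interval is part of the stated hypothesis.

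**What to change.** 1. Reconcile the dates in the Abstract, Study Design, Study Population and Setting, Statistical Analyses and Results, so that the questionnaire window and completion date agree with the 12- and 24-month contacts.
2. Label January 2017 as the analysis of 6-month outcomes, and schedule a second analysis of the 12- and 24-month data after the last contact in June 2018.
3. For relapse-free time and survival, replace the unpaired tests with Kaplan-Meier estimates, log-rank tests and Cox models. Start the clock at the baseline survey, analyse relapse in those in remission at baseline, and add time since diagnosis to the adjustment factors.

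The cost is a change of wording plus completion of contacts that are already scheduled. The downside is that final relapse and survival results arrive about 18 months later (December 2016 to June 2018). Dropout will thin the late data: in May 2016 only 33 of the 101 participants enrolled at least 6 months earlier had completed the 6-month survey. Survival methods handle unequal follow-up, but they do not cure dropout that is related to prognosis.
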